#### SUMMARY Phase I study ([Study CTN B-HIV-1/99](#)):

The Phase I study enrolled 11 HIV-positive subjects, including 9 subjects on ART. Subjects were maintained on ART (if entered on ART); all subjects were treated with 12 immunizations of Vacc-4x at a dose of 0.4 mg/intradermal injection over a period of 26 weeks. Immunizations were performed following injection of rhu-GM-CSF (Leucomax® [molgramostim]) as adjuvant.

*Safety Results:*

All subjects experienced one or more adverse events (AEs); nine subjects experienced events judged as related to treatment. The adverse reactions reported were mild or moderate in severity except for severe local reactions at the injection site in one subject. No subjects were withdrawn due to treatment-related AEs or toxicological reactions; no serious AEs (SAEs) occurred.

*Efficacy Results:*

All subjects experienced a cell-mediated immune response, measured by delayed-type hypersensitivity (DTH) skin reaction. Some cell-mediated immune response, measured by gamma interferon ( $\gamma$ -IFN) release using ELISPOT, was reported for 45% of the subjects; no antibody response to Vacc-4x peptides was observed.

SUMMARY Phase II Study ([Study CTN B-HIV-2/2001](#)):

The Phase II study (CTN B-HIV-2/2001) of Vacc-4x enrolled 40 HIV- positive subjects, of which 38 completed the trial. This was a dose-finding study where subjects were maintained on ART and treated with 10 immunizations at a dose of 0.4 mg (20 subjects) or 1.2 mg (20 subjects) of Vacc-4x intradermal injection, over a period of 26 weeks. Immunizations with Vacc-4x were performed following injection of rhu-GM-CSF (Leucomax [molgramostim]) as a local adjuvant. ART was interrupted from Week 26 to Week 30 to allow exposure to the subject's own virus (autologous immunization). ART was resumed from Week 30 to Week 38 to allow maturation of immune responses to the Vacc-4x peptides and to the subject's own virus. ART was discontinued from Week 38 to Week 52, when the study was formally concluded.

*Safety Results:*

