## **2.2 Study Endpoints**

### **2.2.1 Efficacy Endpoints**

#### **2.2.1.1 Primary Efficacy Endpoints**

- Viral load set point (mean of VL count Visit 8 and Visit 9) for subjects discontinuing ART according to protocol and *not* resuming ART until Visit 9 compared to:
  - viral load set point\* for subjects not resuming ART before week 52 or later in the CT-BI Vacc-4x 2007/1 study and who entered this study,or if week 52 not reached in the previous study
  - viral load set point\*\* for subjects resuming ART at the earliest week 40 in the CT-BI Vacc-4x 2007/1 study and who entered this study.

*\* The VL set point was defined as the mean of VL count week 48 and week 52 week in subjects who did not resume ART.*

*\*\*The VL set point was defined as the week 40 VL count for subject resuming ART week 40 or the mean of the last two VL counts prior to ART resumption for subjects resuming ART week 44 or later but before week 52.*

Comparison will also be made to pre-ART viral load values, if available from the CT-BI Vacc-4x 2007/1 study.

- T-cell response will be measured by ELISPOT as well as by T-cell proliferative response assay (Flow Cytometry) and intracellular cytokine staining at Visit 2 (before re-boosting), Visit 4 (two weeks after re-boosting), Visit 6, Visit 9 and Visit 10. These will be compared to the responses reported in the study CT-BI Vacc-4x 2007/1.

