### **7.2.5 T-cell Response**

Blood samples (approximately 60 mL) will be drawn and the peripheral blood lymphocytes (PBL) separated at each clinical trial site. The PBL will be frozen at  $< -70^\circ\text{C}$  and shipped frozen within 21 days of collection to the central laboratory in Europe (Lausanne, Switzerland) for evaluation. Handling of samples at the site will be detailed in laboratory manuals. The T-cell response to the p24 antigen (including Vacc-4x peptides) will be measured using an ELISPOT test, T-cell proliferation and intracellular cytokine staining at Visit 2, 4, 6, 9 and 10 (End of Study).

ELISPOT is a sensitive immunoassay that will enable detection of antigen-specific T-cells generated after Vacc-4x re-boosting compared with Visit 2 (before re-boosting).

Blood samples will also be analyzed by flow cytometry. Collected cells will be labeled with fluorescent dye (carboxyfluorescein succinimidyl ester [CFSE]), and upon antigen-challenge, activity (intracellular cytokines/ biomarkers, proliferation, T-cell receptor repertoire, surface activation markers) of antigen-specific cells will be visualized and quantified.

T-cell proliferative responses will be evaluated using the T-cell proliferation assay modeled after a previously reported assay ([Kvale, 2005](#)). T-cell proliferative responses will be compared with data reported in the initial study CT-BI Vacc-4x 2007/1 (EudraCT Number 2007-006302-13).

Results for intracellular cytokine testing will be presented in a single written report appended to the Clinical Study Report, to be prepared by the central laboratories. These outputs will be supplied directly to the Sponsor.

In addition, supernatant from the T-cell proliferation assay will be collected for further possible biomarker (e.g., cytokines) testing by Bionor Immuno AS in order to depict Vacc-4x induced T-cell responses. A single written report appended to the Clinical Study Report will be performed by Bionor Immuno AS.

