## **10.6.2 Efficacy Analysis**

### **10.6.2.1 Primary Efficacy Endpoints**

The primary efficacy endpoint of this study is the comparison of the re-boost viral load set-point (definition given in Section 2.2.1.1) after re-boosting and a 16 week ART-free period with the viral load set-point (definition given in Section 2.2.1.1) reported in the initial CT-BI Vacc-4x 2007/1 study (EudraCT Number 2007-006302-13). The primary comparison will be a Wilcoxon signed rank test comparing changes in viral load between the two stated comparison values. The re-boost viral load set-point will also be compared to the pre-ART viral load value, if available from the study CT-BI Vacc-4x 2007/1.

Note: For the reporting of this viral load endpoint, viral load values may have an appropriate transformation (e.g. log base 10) applied prior to endpoint derivation and subsequent analysis.

The co-primary endpoint of this study is the T-cell response (binary outcome: response Yes/No) to Vacc-4x and/or p24 which will be measured by ELISPOT as well as by T-cell proliferative response assay (flow cytometry) and intracellular cytokine staining at Visit 2 (before re-boosting), Visit 4 (two weeks after re-boosting), Visit 6, 9 and 10 (End of Study). These responses will be compared to the T-cell response reported in the initial study CT-BI Vacc-4x 2007/1 (EudraCT Number 2007-006302-13) using McNemar's test. Definition of positive responses will be defined in the statistical analysis plan (SAP).

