### **10.6.2.2 Secondary Efficacy Endpoints**

The following endpoints (based on continuous data types) will be compared (for within subject comparisons) using the Wilcoxon signed rank test:

- CD4 counts at all visits, absolute numbers, and treatment emergent changes from the mean of Screening and Visit 2 data.
- Change (and percent change) in CD4 count from Visit 5 (discontinue ART) to Visit 6, 7, 8, 9 and 10 (End of Study).
- CD8 counts at all visits, absolute numbers, and treatment emergent changes from the mean of Screening and Visit 2 data.
- Change (and percent change) in CD8 count from Visit 5 (discontinue ART) to Visit 6, 7, 8, 9 and 10 (End of Study).

For each individual subject both the absolute and relative changes in CD4 and CD8 values registered at Visit 9) will be compared with the corresponding values registered at Week 28 (ART discontinued) and Week 52 (or last visit before ART re-initiation) in the initial study CT-BI Vacc-4x 2007/1 (EudraCT Number 2007-006302-13).

- DTH (both induration and erythema) at Visit 2 and Visit 4, in terms of observed areas (mm^2 length x height), areas at Visit 2 will be compared with the corresponding values registered at Visit 4. In addition the values for these DTH parameters at Visit 4 will be compared with the DTH responses reported at Week 18 in the initial study CT-BI Vacc-4x 2007/1 (EudraCT Number 2007-006302-13).

The following endpoints (based on binary data types) will be compared (for within subject comparisons) using McNemar's test:

- DTH (both induration and erythema) at Visit 2 and Visit 4, in terms of a positive test, defined as an area  $\geq 10\text{mm}^2$ . The number of positive tests registered at Visit 2 will be compared with the corresponding values registered at Visit 4. In addition the values for these DTH parameters at Visit 4 will be compared with the DTH responses reported at Week 18 in the initial study CT-BI Vacc-4x 2007/1 (EudraCT Number 2007-006302-13).

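### The T-cell co-primary is tested only against the initial study, so it cannot show whether a difference at Visit 4 arose after the re-boost or was already there at Visit 2

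*Protocol*

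**What the plan says.** Section 10.6.2.1 defines the endpoint: "The co-primary endpoint of this study is the T-cell response (binary outcome: response Yes/No) to Vacc-4x and/or p24", measured by ELISPOT, a proliferation assay and intracellular cytokine staining. It continues: "These responses will be compared to the T-cell response reported in the initial study CT-BI Vacc-4x 2007/1", "using McNemar's test. Definition of positive responses will be defined in the statistical analysis plan (SAP"). No other comparator or test is given for this endpoint.

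Section 2.2.1.1 sets the sampling as "intracellular cytokine staining at Visit 2 (before re-boosting), Visit 4 (two weeks after re-boosting), Visit 6, Visit 9 and Visit 10" and then says: "These will be compared to the responses reported in the study CT-BI Vacc-4x 2007/1". The synopsis also names only the initial study. None of these places says which visit of the initial study supplies the reference.

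Two other places treat Visit 2 differently. Section 7.2.5 describes ELISPOT as enabling "detection of antigen-specific T-cells generated after Vacc-4x re-boosting compared with Visit 2 (before re-boosting"). For DTH area, Section 10.6.2.2 states that "areas at Visit 2 will be compared with the corresponding values registered at Visit 4"; it does the same for DTH positivity by McNemar's test, and in both cases adds a comparison of Visit 4 with Week 18 of the initial study.

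Objective (b) in Section 2.1.1 asks whether a re-boost could raise the immune response above that obtained in the initial study.

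**The concern.** The study has no control arm (Section 10.2), and an unspecified interval separates the initial-study sample from Visit 2. By Section 4.2 every subject stopped ART at Week 28 of the initial study and need not have restarted it. Section 1.4 gives a median set point of 22300 copies/ml (n = 56) in Vacc-4x subjects who stayed off ART to Week 52 of that study. T-cell responses could therefore have moved before the re-boost, upwards through exposure to virus or downwards through waning.

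A Visit 4 difference from the initial study combines that earlier movement with whatever followed the re-boost. If the co-primary result is read as showing what the re-boost did, a rise already present at Visit 2 may be credited to it, or a recovery after waning may go unseen. The Visit 2 sample that would separate the two is drawn but is not used for this purpose in the stated analysis.

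**Working it through.** The plan states no power, response rate or effect size for this endpoint, so there is no figure to reproduce. Section 10.1 gives 30 to 40 subjects as a feasibility estimate, and Section 10.6 sets two-sided p < 0.05.

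**Exact McNemar test.** With b changes from negative to positive and c from positive to negative, p = min(1, 2 × P[X ≤ min(b, c)]), X ~ Binomial(b + c, 1/2). If all discordant pairs go one way, p = 2 × (1/2)^m:

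- m = 5: 2/32 = 0.0625
- m = 6: 2/64 = 0.031
- m = 7: 2/128 = 0.016

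**Two constructed patterns, six subjects each, everyone else unchanged.**

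| Pattern | Visit 2 vs initial (planned) | Visit 4 vs initial (planned) | Visit 4 vs Visit 2 (not planned) |
|---|---|---|---|
| Six turn positive before Visit 2 and stay positive | 6 up, p = 0.031 | 6 up, p = 0.031 | no discordant pairs, p = 1 |
| Six wane before Visit 2 and are restored at Visit 4 | 6 down, p = 0.031 | no discordant pairs, p = 1 | 6 up, p = 0.031 |

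In the first row Visit 4 is significant with no re-boost effect. In the second a change after the re-boost leaves no trace at Visit 4 against the initial study.

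**Why the two planned tests do not replace the missing one.** Suppose five subjects convert before Visit 2 and one more by Visit 4. Visit 2 vs initial gives p = 0.0625 and Visit 4 vs initial gives p = 0.031, which looks like an effect appearing after the re-boost. Visit 4 vs Visit 2 has one discordant pair: p = 2 × (1/2) = 1.

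**Rejection probabilities under assumed rates.** The response rates and a within-subject correlation ρ of 0.2 to 0.4 are assumptions, not protocol figures. With marginal rates p1 and p2, P(both positive) = p1·p2 + ρ√[p1(1−p1)p2(1−p2)]; the discordant probabilities are p1 and p2 minus that. For example, rates 0.3 and 0.6 with ρ = 0.2 give 0.18 + 0.2 × 0.2245 = 0.225, so 0.075 change down and 0.375 up. Summing the exact test over all outcomes gives:

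| Assumed rates: initial / Visit 2 / Visit 4 | Test | n = 30 | n = 40 |
|---|---|---|---|
| 60% / 30% / 60% | Visit 2 vs initial (decline) | 64–79% | 80–92% |
| | Visit 4 vs initial | 2.0–2.4% | 2.4–2.8% |
| | Visit 4 vs Visit 2 | 64–79% | 80–92% |
| 50% / 80% / 80% | Visit 2 vs initial (rise) | 68–83% | 84–94% |
| | Visit 4 vs initial (rise) | 68–83% | 84–94% |
| | Visit 4 vs Visit 2 | 1.2–1.8% | 1.8–2.3% |

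These figures show what each test responds to. They do not estimate how likely either pattern is in this cohort.

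**The case against.** The strongest reply is that the comparator is the right one for the stated objective. Objective (b) asks about the level reached in the initial study. A responder who wanes and is restored to that level has not exceeded it, so a concordant pair is the correct answer. That stands, and it is why the comparison should remain.

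The second reply is that Visit 2 is itself among the visits compared with the initial study, so drift would be visible. The Visit 2 rows above bear this out: in both patterns the planned Visit 2 test registers the movement. This answers the objection only in part, because a reader would have to infer the re-boost effect from two tests against a shared reference, which can mislead as the five-then-six example shows.

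Third, Section 7.2.5 already names Visit 2 as an ELISPOT reference, and a supporting analysis may exist in the SAP, which is not at hand. But Section 7.2.5 describes one of three assays and sets no test. Section 10.6.2.1 defers the definition of a positive response to the SAP, not the comparator.

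Fourth, the mechanism is uncertain. A reader might infer that the protocol itself calls these subjects' exposure to virus an immunization. It does not: "ART was interrupted from Week 26 to Week 30 to allow exposure to the subject's own virus (autologous immunization") in Section 1.4 describes a planned interruption in a different trial, CTN B-HIV-2/2001. The initial-study reference visit is also unnamed; if it falls late in the ART-free period, rebound exposure is already partly or wholly in the reference.

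**Conclusion.** The gap is real but limited. As written, every T-cell visit, including the pre-re-boost one, is tested only against the initial study. That answers objective (b) but not whether a Visit 4 difference arose after the re-boost. The minimum case is small: six one-way conversions before Visit 2, out of 30 to 40 subjects, suffice for p = 0.031 at Visit 4 without any re-boost effect.

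A reader might go further and conclude that the co-primary is biased or uses the wrong reference. The documents do not support that. The reference matches objective (b), the protocol gives no size for waning or viremia-driven change in this cohort, and the planned Visit 2 comparison would reveal drift indirectly. The conclusion rests on the protocol's analysis text alone and assumes only that drift between the studies cannot be taken as zero.

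**What to change.** Keep the initial-study comparison as the test of objective (b). In Sections 2.2.1.1 and 10.6.2.1 and in the synopsis, add a within-subject Visit 2 versus Visit 4 McNemar test of T-cell response, in line with Section 10.6.2.2 for DTH and with what Section 7.2.5 implies for ELISPOT. State that an increase will be attributed to the re-boost only where this contrast supports it. The synopsis statistical methods text lists Visit 5 where Section 10.6.2.1 and Table 1 place the T-cell sample at Visit 4; these must be reconciled in the same edit.

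The cost is wording in three places and one more paired analysis per assay, three in all. No extra sampling is needed: both visits are in Table 1 and all samples go to the same central laboratory (Section 7.2.5). The added contrast has limits. It remains an uncontrolled before-after comparison, though over about four weeks (Day 1 to Day 28 ± 2) rather than the whole gap between studies. As a binary test it is silent on further increases in subjects already positive at Visit 2. Conversions already present at Visit 2 would no longer count in favour of the re-boost.

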### **10.6.2.2 Secondary Efficacy Endpoints**

The following endpoints (based on continuous data types) will be compared (for within subject comparisons) using the Wilcoxon signed rank test:

- CD4 counts at all visits, absolute numbers, and treatment emergent changes from the mean of Screening and Visit 2 data.
- Change (and percent change) in CD4 count from Visit 5 (discontinue ART) to Visit 6, 7, 8, 9 and 10 (End of Study).
- CD8 counts at all visits, absolute numbers, and treatment emergent changes from the mean of Screening and Visit 2 data.
- Change (and percent change) in CD8 count from Visit 5 (discontinue ART) to Visit 6, 7, 8, 9 and 10 (End of Study).

For each individual subject both the absolute and relative changes in CD4 and CD8 values registered at Visit 9) will be compared with the corresponding values registered at Week 28 (ART discontinued) and Week 52 (or last visit before ART re-initiation) in the initial study CT-BI Vacc-4x 2007/1 (EudraCT Number 2007-006302-13).

- DTH (both induration and erythema) at Visit 2 and Visit 4, in terms of observed areas (mm^2 length x height), areas at Visit 2 will be compared with the corresponding values registered at Visit 4. In addition the values for these DTH parameters at Visit 4 will be compared with the DTH responses reported at Week 18 in the initial study CT-BI Vacc-4x 2007/1 (EudraCT Number 2007-006302-13).

The following endpoints (based on binary data types) will be compared (for within subject comparisons) using McNemar's test:

- DTH (both induration and erythema) at Visit 2 and Visit 4, in terms of a positive test, defined as an area  $\geq 10\text{mm}^2$ . The number of positive tests registered at Visit 2 will be compared with the corresponding values registered at Visit 4. In addition the values for these DTH parameters at Visit 4 will be compared with the DTH responses reported at Week 18 in the initial study CT-BI Vacc-4x 2007/1 (EudraCT Number 2007-006302-13).

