No safety concern was raised during this study. No SAEs were reported during the period of immunization. One subject experienced a transient vasovagal reaction in conjunction with immunization and the DTH test at Week 26 and Week 38. A second subject experienced a vasovagal reaction in conjunction with the DTH test at Week 52. For the laboratory parameters, vital signs, and performance status, no changes attributable to immunization were observed. Changes in HIV ribonucleic acid (RNA), CD4 cell counts, and CD8 cell counts showed no safety concerns related to immunization.

*Efficacy Results:*

Immunological responses reported as DTH-positive reactions were observed for all subjects. Overall, positive responses both for induration and erythema were statistically significantly higher in the high dose (HD, 1.2 mg Vacc-4x) group compared to the low dose (LD, 0.4 mg Vacc-4x) group. The dose-dependent differences in DTH reactions were maintained throughout the study. T-cell proliferation appeared stable after Week 12 and demonstrated an HD advantage, consistent with the DTH results. ART was interrupted at Week 38 with planned re-start when CD4 counts fell to less than 200/ $\mu$ L or when AIDS- or HIV-related events were observed (i.e. clinical practice). DTH responses to Vacc-4x (high versus low response determined at Week 38) were associated with reduced viral loads and correspondingly improved CD4 counts at the end of the study (Week 52).

During the immunization period, CD4 counts were stable or increased. Interruption of ART resulted in reduction of CD4 counts. However, 14 weeks after the last interruption of ART (Week 52), the mean CD4 counts were still above  $200 \times 10^6$  cells/L. No difference between the LD and the HD groups was observed. The majority of subjects remained off ART following completion of the study (Week 52); permission was given to follow the subjects until they resumed ART. The duration of treatment interruption was linked to immune responsiveness to the peptides. When study subjects were compared to similar subjects in the Netherlands that had stopped treatment without immunotherapy, a significantly slower decline in CD4 cells was noted for the Vacc-4x subjects. The median treatment interruption achieved for all subjects that participated in the Vacc-4x Phase II clinical study was 31 months.

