#### **2.1.2 Secondary Objectives**

- To evaluate the effect of a re-boost with Vacc-4x on CD4 counts and CD8 counts.

- To assesses *in vivo* immunogenicity of Vacc-4x by evaluation of DTH and to compare the DTH response to the DTH response observed in the initial study; CT-BI Vacc-4x 2007/1 (EudraCT Number 2007-006302-13).
- To evaluate the safety and tolerability of re-boosting with Vacc-4x.

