### **10.2 Randomization Codes**

This is a non-randomized study.

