#### **10.6 Statistical Methods**

In general continuous variables will be described using number of observations (n), mean, standard deviation (SD), geometric mean, minimum, maximum, median, and quartiles. Categorical data will be presented using counts (n) and percentages (%).

All statistical analyses will be performed using appropriate procedures in SAS Software Version 9.2 or higher. Significance of effects will be determined by two-sided tests with p-value < 0.05.

All analyses will be carried out after all participants have completed Visit 10 (or early withdrawal from study) and the study database has been authorized by the Sponsor as complete and final, and protocol deviations have been identified.

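### In subjects who stop ART at Visit 5, the within-study signed rank tests of CD4 change to Visits 6-9 measure ART interruption plus any re-boost effect, so they cannot show a re-boost effect

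*Protocol*

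**What the plan says.** The objective in Section 2.1.2 is "To evaluate the effect of a re-boost with Vacc-4x on CD4 counts and CD8 counts". Section 10.6.2.2 gives a list of continuous secondary efficacy endpoints that "will be compared (for within subject comparisons) using the Wilcoxon signed rank test". The list includes "CD4 counts at all visits, absolute numbers, and treatment emergent changes from the mean of Screening and Visit 2 data", then "Change (and percent change) in CD4 count from Visit 5 (discontinue ART) to Visit 6, 7, 8, 9 and 10 (End of Study"), and the same two constructions for CD8, the second being "Change (and percent change) in CD8 count from Visit 5 (discontinue ART) to Visit 6, 7, 8, 9 and 10 (End of Study").

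Section 10.6 sets the rule for reading the tests: "Significance of effects will be determined by two-sided tests with p-value < 0.05". There is no concurrent control; Section 10.2 states "This is a non-randomized study".

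On what happens to CD4 without ART, Section 1.4 says of the earlier Phase II study CTN B-HIV-2/2001: "Interruption of ART resulted in reduction of CD4 counts". It gives no size or SD. Section 1.4 also says that in the initial study (CT-BI Vacc-4x 2007/1) the percentage CD4 change from Week 28 to the last value before ART resumption did not differ between vaccine and placebo.

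Sections 2.2.1.2 and 10.6.2.2 further plan a same-subject comparison of the CD4 and CD8 changes at Visit 9 with Week 28 and Week 52 (or the last visit before restart) of the initial study.

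**The concern.** A signed rank test on a within-subject change normally asks whether the change is centred on zero. That fits the objective only if zero change is what an ineffective re-boost would produce. Between Visit 5 and Visits 6-9, ART is stopped in eligible subjects who are taking it. By the protocol's own account CD4 then falls, so an ineffective re-boost predicts a fall. The same holds for changes from the mean of Screening and Visit 2 to Visits 6-9 in subjects who were on ART at that baseline.

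This has two consequences for CD4. A significant fall cannot be credited to the re-boost or blamed on it. And a re-boost that preserves CD4 moves the change towards zero, so the better it works, short of producing a net gain, the less likely the test is to be significant. Under the general significance rule, an effect of stopping ART could be reported under an efficacy heading, while a real benefit could appear as a null result that is indistinguishable from low power.

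**Working it through.** **No plan figure to reproduce.** Section 10.1 estimates that 30 to 40 subjects will be eligible. It states no effect size, SD or power.

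**Inputs from the protocol.** Two-sided 0.05 (10.6); Wilcoxon signed rank, within subject (10.6.2.2); n = 30 to 40 (10.1), with n = 20 added in case fewer stop ART; direction of CD4 change off ART is downward (1.4).

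**Assumptions.** The mean natural fall is d, in units of the SD of the change, with d from 0.2 to 1.0. For scale, a fall of 100 x10^6/L with an SD of 150 is 100/150 = 0.67. The re-boost removes a fraction a of the fall. Individual changes are Normal(-d(1-a), 1). Rejection rates come from simulation with 4,000 runs per cell.

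**Step 1: re-boost does nothing (a = 0).**

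| d | n=20 | n=30 | n=40 |
|---|---|---|---|
| 0 | 4.5% | 5.2% | 4.8% |
| 0.2 | 12.6% | 18.2% | 22.1% |
| 0.33 | 27.3% | 39.8% | 50.8% |
| 0.5 | 53.2% | 73.2% | 85.7% |
| 0.67 | 77.9% | 93.4% | 98.0% |
| 1.0 | 98.6% | 100% | 100% |

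The d = 0 row shows that the test is valid for its own null. As a check, Phi(d√n - 1.96) at n = 30, d = 0.67 is Phi(3.67 - 1.96) = 95.6%, close to the simulated 93.4%.

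**Step 2: when does rejection exceed 50%?** Approximately when d > 1.96/√(3n/π). At n = 30 this is 1.96/5.35 = 0.37. It is 0.32 at n = 40 and 0.45 at n = 20.

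**Step 3: direction.** At n = 30 and d = 0.67, a = 0, 25, 50, 75 and 100% gives rejection of 93%, 74%, 41%, 13% and 5%. Greater CD4 benefit gives fewer significant results.

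**Step 4: subjects already off ART at Visit 5.** Give them an assumed natural fall of 0.1 SD and the others 0.67 SD. At n = 30, null rejection drops from 93% to 76% if they are 25% of the sample, and to 49% if they are 50%.

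**Step 5: CD8.** The protocol gives no direction. If stopping ART raised CD8 by 0.5 SD, rejection at n = 30 with no re-boost effect would be 75%. It would be 97% if the re-boost added 0.25 SD and 25% if it subtracted 0.25 SD. Attribution fails either way, but the pattern in Step 3 does not carry over.

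**Step 6: the contrast with the initial study.** Per subject, take the off-ART change now minus the off-ART change then, with the same expected natural change in both periods. With no re-boost effect, rejection is 4.6% to 5.2% at n = 30 to 40. With a correlation of 0.5 between the two changes (assumed), n = 30 and the same five values of a, it is 5%, 26%, 74%, 97% and 99.9% at d = 1.0, and 5%, 9%, 26%, 51% and 75% at d = 0.5. Power now rises with benefit.

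**Step 7: time off ART must match.** Visit 5 to Visit 9 is day 84 to day 196: 112 days, or 16 weeks. Week 28 to Week 52 is 24 weeks. If, purely for illustration, the fall were proportional to time, the 16-week fall would be 16/24 = two thirds of the 24-week fall. An ineffective re-boost would then show a difference of one third of the 24-week fall, in the direction of benefit. The 16-week counterpart is Week 28 + 16 = Week 44.

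**The case against.** The strongest reply is that the protocol never says these changes are tested against zero. Section 10.6.2.2 speaks only of within-subject comparison, and the synopsis says the secondary endpoints are compared with results from the initial study. The zero null is an inference, and should be called one. It remains the natural reading: the cross-study comparison has its own paragraph, tied to Visit 9, and no comparator is named for the Visit 5 to Visit 6, 7, 8 and 10 changes. If another null is meant, the text still needs to say so.

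A second reply is that Section 10.5.2 promises efficacy subgroups by time on or off ART, with detail left to the SAP. Those subgroups choose subjects or data; they do not change the null. Restricting to subjects who stop ART makes the mismatch sharper.

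A third is that these are secondary endpoints in an open, single-group study with no decision rule attached, and that the label itself mentions ART discontinuation. That limits the consequence but does not make the p-value informative about the re-boost.

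Several stronger readings are tempting and not supported. A reader might infer that these tests will usually be significant; that depends on a fall and SD the protocol does not give, and at 0.2 SD rejection is only about 18% to 22% at n = 30 to 40. A reader might extend the reversed direction to CD8; the documents state neither how CD8 moves off ART nor which direction is benefit. A reader might treat the whole endpoint as on-ART against off-ART; Visit 10 comes eight weeks after the recommended restart, and Section 3.1 and Table 1 allow subjects to be off ART already. And a reader might conclude that a suitable off-ART comparison is missing; it is planned for Visit 9, though not at matched time off ART.

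**Conclusion.** The point holds for CD4 at Visits 6-9 in subjects who stop ART at Visit 5, whether the change is taken from Visit 5 or from an on-ART Screening/Visit 2 mean. On the natural zero-change reading, the test cannot separate the re-boost from ART interruption, and it loses rejections as CD4 preservation improves, short of a net gain. With no re-boost effect and 30 subjects, false attribution ranges from about 18% to 93% for assumed mean falls of 0.2 to 0.67 SD; only the downward direction of the fall comes from the protocol. For CD8 the conclusion is limited to attribution. Visit 10 is a different comparison, after restart, and should be treated as such. The correction should be made, but it does not touch the primary endpoints.

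**What to change.** In Section 10.6.2.2 and the matching synopsis text:

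- Report the CD4 and CD8 changes from on-ART references to Visits 6-10 as median change with 95% CI, labelled as the response to ART interruption (Visits 6-9) and to restart (Visit 10). Count no signed rank test of them as evidence of re-boost efficacy.
- Limit the within-study signed rank test to the change from the mean of Screening and Visit 2 to Visits 4 and 5, in subjects whose ART status does not change over that interval.
- Base off-ART inference on the already planned same-subject contrast with the initial study, in subjects who stopped ART in both studies, at matched time off ART: Visit 5 to Visit 9 against Week 28 to Week 44 where available, not Week 52. For early restarters, use the last pre-restart value at the same time off ART in both studies.
- State that this contrast remains historical and unrandomised.

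The cost is a wording change in the protocol and the matching SAP text, with no new visits, samples or subjects. Some p-values become estimates with intervals, and subjects without a matched value drop out of the contrast.
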